## BACKGROUND

As described in the main protocol the Bisoprolol in COPD Study (BICS) is a pragmatic multicentre randomised double-blind placebo-controlled trial investigating the clinical and cost-effectiveness of adding bisoprolol to usual COPD therapies in patients with COPD at high risk of exacerbation.

Whilst BICS will definitively address the question of the clinical effectiveness of beta-blockers in reducing exacerbations in all patients with COPD who do not currently fulfil the criteria for beta-blocker therapy, there remains the important question as to the mechanism by which beta-blockers reduce exacerbations and whether beta-blocker therapy should be targeted at a readily identifiable sub-group of COPD patients.

The aim of the cardiac investigation sub-study is to risk stratify BICS participants for undiagnosed and clinically relevant cardio-vascular pathology in order to test the hypothesis that any benefits of beta-blocker therapy on COPD exacerbations are restricted to those COPD patients at high risk of occult undiagnosed heart disease.

## SUB-STUDY OBJECTIVES

### Primary Objective

To determine if any clinical success of beta-blocker therapy in COPD patients is restricted to those COPD patients at high risk of occult undiagnosed heart disease.

### Secondary Objectives

To determine the best combination of biomarkers±echocardiography-derived parameters that reliably identifies the subgroup of COPD patients who will benefit from beta-blocker therapy for the purposes of COPD treatment.

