| Outcome measures               | Primary and secondary outcomes as per BICS.                                                                                                                                                                                                                                                                                                                                                                                                                                                                                                                                                                                                                                                                                                                                                                                                                                                                                                                                                                                                                                                                                                                                                                                                                                                                                                                                                                                                                                                                                                                                                                                                                                                                      |

|                     |                                                                                                                         |
|---------------------|-------------------------------------------------------------------------------------------------------------------------|
|                     | The sub-study outcome measures will be NT-proBNP, hs-TnI, hs-CRP, Galectin and echocardiography parameters.             |
| Statistical methods | Participants will be risk stratified for occult heart disease and analysed as sub-groups within the main BICS analysis. |

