### **Echocardiography:**

Echocardiography. The echocardiography will be arranged at a convenient time for the participant and the imaging centre – it will either be arranged by a member of the cardiology research team or a member of the BICS research team. Echocardiography would be ideally timed with the initial blood investigations, within 12 weeks from randomisation, however echocardiography may be delayed by exacerbations if the participant exacerbates after joining the study. Echocardiography will be performed according to standard protocols on GE or Philips systems, inclusive of diastolic function, speckle and tissue Doppler imaging for off line analysis. Apical 2,3 and 4 CV will be acquired for accurate computation of EF and atrial volumes. Left ventricular wall thickness derived from Echocardiography will only be used in the detection algorithm for heart failure with preserved ejection fraction. In addition, an estimated Pulmonary artery pressure, tissue Doppler imaging of the mitral and tricuspid annuli and longitudinal, circumferential and radial strain analysis will be derived. Echocardiographs will be identified by study number and, to facilitate any clinical reporting, the participant's name. Echocardiographs will be sent to Aberdeen for analysis by a member of the cardiology research team. Analysis of echocardiographs will only be undertaken after the participant has completed 12 month follow-up (ie after

participant involvement in the trial has finished). Any significant or clinically relevant findings that are likely to significantly impact on the patient's health or future prognosis will be provided to the participant's GP (with the participant's agreement).

Timing of blood samples and echocardiography in patients who are exacerbating  
Baseline blood sampling and echocardiography should not be performed within 4 weeks of recovery from an exacerbation of COPD. If the participant experiences prolonged period(s) of exacerbation during titration, the 12 week window can be extended to permit the participant to take part in the sub-study. If the participant has an exacerbation when the blood/echocardiography are due, the 12 week window can be extended to permit the participant to take part in the sub-study.

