## PROPOSED ANALYSES

Predefined cutoffs will be used to risk stratify sub-study participants for occult, previously undiagnosed heart disease:

Hs TnI levels will be analysed using cutoffs that we have shown to be highly predictive in detecting subjects at high risk of silent cardiac target organ damage.

Pre-determined imaging cut-offs for in defining "occult, previously undiagnosed heart disease:

- Echo bi-plane LV EF<40% with dilated or non-dilated LV.
- Heart failure with mid-range EF (40-49%) for as per most recent ESC guidelines
- Heart failure with preserved EF ( $\geq 50\%$ ) who additionally have, as per ESC guidelines:
  - either NT-proBNP $\geq 125$  pg/ml
  - or with evidence of diastolic dysfunction (defined as abnormal LV relaxation by Doppler imaging, ie E/E' $>13$  or echo-enhanced left atrial volume $>34$  ml/m^2 or left ventricular hypertrophy diagnosed as LV mass index  $\geq 115$  g/m^2 for males and  $\geq 95$  g/m^2 for females. If current guidelines are superseded during the course of the study, the diagnostic criteria described in these will be used.

Statistical analyses will be according to the intention to treat principle. The primary outcome of number of COPD exacerbations requiring antibiotics and/or oral corticosteroids in the 12 month study period will be compared between randomised groups overall and in each subgroup (high and low risk occult heart disease) using negative binominal regression with length of time in study as an offset. To assess which biomarkers, their optimal cut-offs and/or which imaging outcome is the best method of identifying those most likely to benefit we will use ROC analysis along with sensitivity and specificity of the specific biomarker and imaging outcomes in identifying those which will show benefit. Benefit will be defined as no exacerbations during follow-up. We may

use logistic regression to assess which biomarkers/imaging measurements are best predictive alone or in combination of a beneficial outcome in terms of a reduction in COPD exacerbations.

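### Appendix 6 chooses markers and optimal cut-offs by ROC in a single cohort and states no internal validation, so the accuracy it reports, if followed as written, will be biased upward

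*Protocol*

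**What the plan says.** All of the relevant text is in Appendix 6 of the protocol.

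- **Secondary Objectives** seek the best combination of biomarkers, with or without echocardiographic parameters, that "reliably identifies the subgroup of COPD patients who will benefit from beta-blocker therapy for the purposes of COPD treatment".
- **Proposed Analyses** use ROC analysis to assess which biomarkers, "their optimal cut-offs and/or which imaging outcome is the best method of identifying those most likely to benefit". This is reported "along with sensitivity and specificity of the specific biomarker and imaging outcomes in identifying those which will show benefit". The investigators may also "use logistic regression to assess which biomarkers/imaging measurements are best predictive alone or in combination of a beneficial outcome".
- **The outcome for this search** is given in the same section: "Benefit will be defined as no exacerbations during follow-up".
- **The candidates** are named in the Synopsis: "The sub-study outcome measures will be NT-proBNP, hs-TnI, hs-CRP, Galectin and echocardiography parameters". The Echocardiography section lists what the scans will yield, including ejection fraction, atrial volumes and an estimated pulmonary artery pressure, and adds that "tissue Doppler imaging of the mitral and tricuspid annuli and longitudinal, circumferential and radial strain analysis will be derived".
- **The cohort** is a single group of about 900 participants (Number of participants). Sites without echocardiography may contribute blood samples only (Sub-study design).
- **The main sub-study comparison** is handled differently: "Predefined cutoffs will be used to risk stratify sub-study participants for occult, previously undiagnosed heart disease". High-risk and low-risk groups are then compared by negative binomial regression.

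**The concern.** When several markers are searched, a cut-off is tuned for each, and the winner's sensitivity and specificity are read from the same data, the result includes whatever chance favoured the winner. The more candidates and the fewer participants with the outcome, the larger that share. A logistic model combining many markers has the same problem.

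Appendix 6 specifies such a search and names no split sample, cross-validation, bootstrap correction or second cohort. Followed as written, it returns a best marker and cut-off with better-than-chance apparent accuracy whether or not anything predicts. The Background of Appendix 6 asks whether treatment should be targeted at a readily identifiable subgroup. Inflated accuracy for a candidate identifier would therefore bear on a question that readers care about.

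**Working it through.** **The plan's own figure.** Appendix 6 claims 80% power with 900 participants, 10% stopping medication, and rates of 2.22 against 1.70 when half are high risk. Per arm, n = 900 × 0.9 × 0.5 / 2 = 202.5. With SD 1.86, z = 0.52 / (1.86 × √(2/202.5)) - 1.96 = 2.81 - 1.96 = 0.85, which is 80.3% power. The other three rows give 80.1%, 80.2% and 80.1%. The figure reproduces, but it concerns the comparison with predefined cut-offs. Appendix 6 gives no sizing for the marker search.

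**How many participants have the outcome.** Assume a negative binomial count with the protocol's mean 2.22 and SD 1.86:

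- shape k = 2.22² / (1.86² - 2.22) = 3.98
- P(no exacerbations) = (k / (k + 2.22))^k = 0.171
- expected number: 900 × 0.171 ≈ 154 in both arms, or 450 × 0.171 ≈ 77 in one arm

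**How many candidates.** The protocol fixes four blood markers: NT-proBNP, hs-TnI, hs-CRP and Galectin. It does not fix the number of echo measures. An upper count from the Echocardiography and Proposed Analyses sections is nine: ejection fraction, atrial volume, E/E', pulmonary artery pressure, mitral tissue Doppler, tricuspid tissue Doppler, and three strains. That makes 13. Wall thickness is left out because the protocol reserves it for the algorithm for heart failure with preserved ejection fraction. With 13 candidates there are 154/13 ≈ 12 outcome events per candidate in both arms, and 77/13 ≈ 6 in one arm.

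**Simulation with no true signal.** Each of 1,000 data sets had an outcome with probability 0.171 and K independent normal noise markers. The combined model was a logistic regression on all K. The best single marker was the one with the largest Youden index at its own optimal cut-off. Each selected rule was then applied to fresh noise data.

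| N | K | Combined AUC, mean (5th to 95th percentile) | Best-marker Youden index, mean | On fresh data: AUC; Youden |
|---|---|---|---|---|
| 900 | 4 | 0.547 (0.520 to 0.579) | 0.100 | 0.500; 0.002 |
| 900 | 8 | 0.569 (0.540 to 0.600) | 0.113 | 0.499; 0.000 |
| 900 | 13 | 0.589 (0.560 to 0.622) | 0.120 | 0.501; 0.000 |
| 450 | 4 | 0.566 (0.524 to 0.611) | 0.140 | 0.498; 0.003 |
| 450 | 8 | 0.597 (0.557 to 0.638) | 0.158 | 0.501; 0.000 |
| 450 | 13 | 0.625 (0.582 to 0.667) | 0.169 | 0.500; 0.000 |

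A separate run at N = 900 splits the Youden index into its parts. With four markers the mean sensitivity was 0.579 and specificity 0.521 (0.579 + 0.521 - 1 = 0.100). With 12 markers they were 0.581 and 0.537 (sum less 1 = 0.118).

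**Correlated markers.** With a common correlation of 0.5, N = 900 and K = 13, the best-marker Youden index falls slightly, from 0.120 to 0.116. The combined AUC stays at about 0.59, because a model that enters every marker fits noise equally well whether or not the markers are correlated. It would fall only if near-duplicate measures were left out.

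**The case against.** Four points can be made for the plan.

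1. **Validation may be in the SAP.** The SAP is not shown, and protocol section 10.3 says it governs all analyses. Nothing in Appendix 6 rules out a bootstrap correction, and no sentence says that accuracy will be reported uncorrected from the same participants. That is inferred from the single cohort and from silence. This stands as a limit on the point. It does not remove it, because the protocol does state a procedure, and that procedure taken alone gives a biased number.
2. **The bias is modest.** A reader might infer that pure noise would pass for reliable identification. The figures do not support that. Sensitivity and specificity just above 0.5, and an AUC usually below about 0.62, would not persuade a careful reader. This stands in full.
3. **The main inference is protected.** A reader might infer that the whole sub-study is compromised. It is not: the high-risk against low-risk comparison uses predefined cut-offs, and the search serves only a secondary objective. This also stands.
4. **The size of the search is uncertain.** Combining markers is only something the investigators may do, and listing an echo measure does not mean that it enters the search. With the four blood markers alone, the combined AUC under noise is about 0.55. This stands, and it is why a range is given. In the other direction, blood-only sites mean that any model combining blood and echo may rest on fewer than 900 participants, which increases the bias.

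**Conclusion.** The point holds in a limited form. Applied as written, the ROC search in Proposed Analyses will overstate accuracy for the secondary objective. Under pure noise at N = 900 the AUC is inflated by about 0.05 (four markers) to 0.09 (13 markers), and the best-marker Youden index by 0.10 to 0.12. If the search is run in one arm of about 450, the inflation is about 0.07 to 0.13 and 0.14 to 0.17. The wording of the secondary objective promises more than an unvalidated search can support.

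These figures assume a negative binomial shape, 4 to 13 candidates, the Youden index as the cut-off rule, and no validation elsewhere.

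A separate fault lies in the same section. Benefit is defined as no exacerbations, with no comparison between arms. On the protocol's own mean and SD, about 17% of placebo participants would meet that definition. Correcting for optimism would leave a fair estimate of prognosis, not of treatment benefit.

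**What to change.** **Proposed Analyses.** Add that the data-driven search is exploratory. State that the whole selection (choice of marker, choice of cut-off and any combination) will be repeated in bootstrap samples, and that optimism-corrected AUC, sensitivity and specificity will be reported with intervals. List the candidate measures. Any confirmatory statement should rest on the predefined cut-offs.

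**Secondary Objectives.** Reword the aim as exploring which combination may identify such a subgroup.

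**Cost.** A few sentences in Appendix 6 and a few hours of programming, with no new data and nothing further asked of participants. The downside is that reported accuracy will look less favourable. The definition of benefit needs its own correction, by assessing marker-by-treatment interaction, and this change does not supply it.

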## SUB-STUDY DESIGN

Participants in BICS will adhere to the main BICS study protocol. Within the sub-study, a limited number of additional investigations will be performed during BICS assessment visits to risk stratify participants for occult undiagnosed heart disease.

Participants enrolled into BICS in sites that have agreed to participate in the sub-study and who have agreed to be contacted about further studies, will be invited to take part in the sub-study after they have agreed to take part in the main BICS study. This may be during their BICS recruitment visit or during the dose titration phase. After providing written informed consent participants will undergo echocardiography at a mutually convenient time, ideally during one of the dose titration assessments, but up to 12 weeks following randomisation is acceptable (and can be delayed if the participant exacerbates during this period). Participants will also be invited to provide two 15ml blood samples, one ideally during the dose titration phase, but up to 12 weeks following randomisation is acceptable (and can be delayed if the participant exacerbates during this period) and one at the final assessment visit at the 12 month visit (if face-to-face) or during the down-titration of the study medication.

Note: if sites are unable to offer echocardiography, they can undertake the blood component of the cardiac sub-study. This will be explained to potential participants when they are invited to take part in the cardiac sub-study. If echocardiography becomes available at the site before the participants complete their follow-up within BICS, a late echocardiography could be offered to participants.

## STUDY POPULATION

### Number of participants

Participants enrolled into BICS in sub-study sites will be invited to take part, the aim is to recruit about 900 participants into the cardiac sub-study.

### **Inclusion criteria**

Participants enrolled in BICS who have consented to be approached for further studies.

### **Exclusion criteria**

There are no exclusion criteria.

### **Identification of participants**

Participants enrolled into BICS in secondary care sites will be invited to take part during the dose titration phase. They will be invited by a member of the BICS local study team. If they are potentially interested in taking part, they will be given the patient information leaflet for the BICS Heart Study.

### **Consenting participants**

Written and verbal explanation of the study aims and protocol will be provided detailing the nature of the study, the procedures involved, the known possible side effects and any risks involved in taking part. It will be clearly stated that the individual is free to withdraw from the study at any time for any reason without any prejudice to future care or their participation in the main BICS study, and with no obligation to give the reason for withdrawal.

## **STUDY ASSESSMENTS**

Participants will adhere to the main BICS assessment regimen. After providing written informed consent for the Heart Study, participants will undergo echocardiography and provide two blood samples at mutually convenient times.

### **Blood assays:**

15 ml blood samples will be taken by a member of the BICS research team at the site:

- 1) Within 12 weeks of randomisation, however, this may be delayed if the participant exacerbates after joining the study
- 2) At the final study assessment (approximately week 52) (if taking study treatment), however this may be delayed by exacerbation.

The 15ml sample will be processed into a serum (plain) tube (10ml) and an EDTA tube (5ml).

The tubes will be centrifuged at 1000-2000g for 10 minutes, and the plasma and serum stored in ~1ml aliquots at -70°C ideally within 1 hour of collection. Samples will be stored locally and sent in batches to Aberdeen. All samples will be stored at -70°C. Samples will be identified by study number and not by the participant's name.

One aliquot per participant per time point will be analysed for N-terminal pro-Brain Natriuretic Peptide (NT-proBNP and Galectin, analysis by [name] in Dundee).

One aliquot per participant per time point will be analysed for high sensitive Troponin I and hs-CRP (hs TnI, analysis by [name] in Edinburgh).

All samples will be analysed in the two core labs mentioned above. Any residual material will be retained in Aberdeen (HRA approved tissue bank - NHS Grampian Biorepository).

### **Echocardiography:**

Echocardiography. The echocardiography will be arranged at a convenient time for the participant and the imaging centre – it will either be arranged by a member of the cardiology research team or a member of the BICS research team. Echocardiography would be ideally timed with the initial blood investigations, within 12 weeks from randomisation, however echocardiography may be delayed by exacerbations if the participant exacerbates after joining the study. Echocardiography will be performed according to standard protocols on GE or Philips systems, inclusive of diastolic function, speckle and tissue Doppler imaging for off line analysis. Apical 2,3 and 4 CV will be acquired for accurate computation of EF and atrial volumes. Left ventricular wall thickness derived from Echocardiography will only be used in the detection algorithm for heart failure with preserved ejection fraction. In addition, an estimated Pulmonary artery pressure, tissue Doppler imaging of the mitral and tricuspid annuli and longitudinal, circumferential and radial strain analysis will be derived. Echocardiographs will be identified by study number and, to facilitate any clinical reporting, the participant's name. Echocardiographs will be sent to Aberdeen for analysis by a member of the cardiology research team. Analysis of echocardiographs will only be undertaken after the participant has completed 12 month follow-up (ie after

participant involvement in the trial has finished). Any significant or clinically relevant findings that are likely to significantly impact on the patient's health or future prognosis will be provided to the participant's GP (with the participant's agreement).

Timing of blood samples and echocardiography in patients who are exacerbating  
Baseline blood sampling and echocardiography should not be performed within 4 weeks of recovery from an exacerbation of COPD. If the participant experiences prolonged period(s) of exacerbation during titration, the 12 week window can be extended to permit the participant to take part in the sub-study. If the participant has an exacerbation when the blood/echocardiography are due, the 12 week window can be extended to permit the participant to take part in the sub-study.

